#### Secondary Analysis

Mixed design analysis of variance will be used to compare the two groups' baseline, post-intervention and follow-up scores on all other secondary measures. The two factors will be time and group. Descriptive statistics (i.e. means, or frequencies) will be used to present data related to adverse and serious adverse events by groups. Any apparently significant differences between groups will be analysed for significance using chi square statistics. In an effort to describe the two interventions, the mean number of steps taken per session will be counted in a convenient sub-sample of participants using the step activity monitors. Independent samples t-test statistic will be used to compare the mean number of steps taken per session by the two groups during treatment sessions.

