It is our hypothesis that participants assigned to the MLWP group will demonstrate greater scores in comfortable gait speed and secondary outcome measures at post intervention and follow-up assessments.

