#### Sensitivity Analyses

Sensitivity analyses will be performed to assess the robustness of the results. First, there is likely to be high inter-correlations among all outcomes. We will use multivariate analysis of variance (MANOVA) approach to analyze all outcomes simultaneously. This method accounts for possible correlations among all outcomes and provides for a global assessment of differences between groups with an indication of where differences exist. Second, we will use generalized estimating equations (GEE) [73] to account for possible serial correlation of measurements within a patient overtime. Unlike ordinary linear regression, GEE allows accounting possible correlation of outcome scores for the same patient over time. We will use sensitivity analysis to explore potential clustering of measurements/outcomes from the same patient. The clustering effect, measured by intra-class correlation coefficient, will be assumed to be equal across patients. Sensitivity analysis will also include a between-group comparison of post-intervention comfortable gait speed in participants who completed at least 12 of the 15 training sessions using analysis of variance. Refer to Table 3 for a summary of the planned analyses.

**Table 3 T3:** Summary of planned primary, secondary and sensitivity analyses

*Objective/Variable*	*Hypothesis*	*Outcome measure (type)* *[continuous (c), binary (b)]*	*Method of Analysis*

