**2) Secondary (T2, T3)**			
Secondary outcomes			
a) Fast walking speed	MLWP > BWSTT	Fast Gait Speed (c)	ANCOVA
b) Walking endurance	MLWP > BWSTT	Six minute walk test(c)	ANCOVA
c) Balance and walking related self-efficacy	MLWP > BWSTT	Activities-specific Balance Confidence Scale (c)	ANCOVA
d) Dynamic balance	MLWP > BWSTT	Functional Balance Test(c)	ANCOVA
e) Mobility participation	MLWP > BWSTT	Life Space Questionnaire (c)	ANCOVA
f) Health-related quality of life	MLWP > BWSTT	Stroke Impact Scale 3.0 (c)	ANCOVA
g) Goal attainment	MLWP > BWSTT	Patient Specific Function Scale(c)	ANCOVA
h) Walking participation	MLWP < BWSTT	Mean daily step activity	ANCOVA
i) Training staff requirement	MLWP < BWSTT	Total number of trainers/number of training sessions (c)	T-test
j) Meaningful change in gait speed of ≥ 0.14 m/s	MLWP > BWSTT	Comfortable gait speed change score T2-T1 ≥ 0.14 m/s)(b)	Chi-square test
Adverse events (count)			
a) Falls during session		Therapist report (b)	Chi-square test
b) Injury during session		Therapist report (b)	Chi-square test
c) Falls between session		Patient report (b)	Chi-square test
d) Myocardial Infarction		Patient report/health record (b)	Chi-square test
e) New stroke		Patient report/health record (b)	Chi-square test
f) Hospitalization		Patient report/health record (b)	Chi-square test
g) Death (all causes)		Health record/Physician (b)	Chi-square test

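### The continuous secondary outcomes have two different planned analyses (mixed-design ANOVA in the text, ANCOVA in Table 3), and two parts of the stated hypothesis do not match the table

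*Protocol article*

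**What the plan says.** All references are to the Protocol article.

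- **Secondary Analysis, text.** The method is stated as "Mixed design analysis of variance will be used to compare the two groups", and the data it is applied to are the "baseline, post-intervention and follow-up scores on all other secondary measures". The model is described in one sentence: "The two factors will be time and group". The randomization stratum is not in it, and no term is named as the test of treatment.
- **Table 3, secondary block (T2, T3).** Rows a to h, the continuous outcomes, are assigned ANCOVA. No covariate is given. Row i uses a t-test and row j a chi-square test. The Sensitivity Analyses section presents this table as the summary of what is planned.
- **Abstract.** Groups are compared by ANCOVA, with the gait speed stratum as the only covariate.
- **Hypothesis, end of the Background.** The MLWP group is expected to show "greater scores in comfortable gait speed and secondary outcome measures at post intervention and follow-up assessments".
- **Table 3, comfortable gait speed.** It appears as the primary ANCOVA at T2, as a T2 minus T1 responder outcome (row j), as a completer analysis (row 3c), and within the MANOVA and GEE sensitivity rows (3a, 3b).
- **Table 3, row "h) Walking participation".** The direction for mean daily step activity is MLWP below BWSTT.
- **Completers.** The text compares post-intervention speed "in participants who completed at least 12 of the 15 training sessions using analysis of variance"; row 3c of Table 3 says ANCOVA.

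**The concern.** A mixed ANOVA with baseline as a time level and an ANCOVA do not estimate the same thing. In the first, baseline is a response. The group main effect then averages over a visit at which randomization makes the expected difference zero, and the interaction is a joint 2-df test. In the second, baseline information is a covariate and each visit has its own adjusted difference. Two analysts who each follow the article could report different estimates and p-values for the eight outcomes in rows a to h, and the choice could be made with the results in view.

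The other two mismatches bear on what the trial can claim. The MLWP section defines learning through retention, so the follow-up result on the main measure matters to the trial's own theory; yet the hypothesis about it has no primary or secondary test. For daily steps, the declared direction differs between the hypothesis and the table.

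**Working it through.** **1. The plan's own figure.** Inputs from Sample size: difference 0.14 m/s, SD of change 0.19 m/s, two-sided 0.05, power 80%.
n per group = 2 × (1.960 + 0.842)² × 0.19² / 0.14² = 28.9, so 29. With 17% loss, 29 / 0.83 = 34.9, so 35 per group and 70 in all. The stated figures reproduce, and nothing below alters them.

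**2. Set-up for comparing the methods.** The article gives no effect sizes for rows a to h, so the gait speed scale serves as an illustration. Assumptions: 29 per arm with data at all visits, effect 0.14 m/s at both T2 and T3, equal correlation ρ between visits, SD of change 0.19. The cross-sectional SD is not stated; I take 0.20, 0.25 and 0.30 m/s. From 0.19² = 2 SD²(1 − ρ), ρ = 0.549, 0.711 and 0.799.

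**3. Mixed ANOVA, group main effect.** Expected contrast = (0 + 0.14 + 0.14) / 3 = 0.093 m/s, two thirds of the effect. SD of a participant's three-visit mean = SD × √((1 + 2ρ)/3); SE = that × √(2/29).

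| SD | SD of mean | SE | Power (noncentral t) |
|---|---|---|---|
| 0.20 | 0.167 | 0.044 | 55% |
| 0.25 | 0.225 | 0.059 | 34% |
| 0.30 | 0.279 | 0.073 | 24% |

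Simulation under the same assumptions (4,000 trials per scenario) gave 55%, 34% and 25%.

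**4. Mixed ANOVA, group-by-time interaction.** Deviations from the mean effect are −0.093, 0.047 and 0.047, with sum of squares 0.01307. Noncentrality = (29/2) × 0.01307 / (0.19²/2) = 10.5. On 2 and 112 df, power is 82%, whatever the cross-sectional SD. If only half the effect (0.07) remains at T3, the sum of squares is 0.0098, the noncentrality 7.9 and power 70%.

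**5. ANCOVA at one visit.** Table 3 names no covariate, so there are two versions.
- Own continuous baseline: residual SD = SD × √(1 − ρ²) = 0.167, 0.176, 0.180; power 88%, 85%, 83% (simulated 87%, 84%, 83%).
- Two-level stratum only, as in the Abstract, approximated by a median split: residual SD = SD × √(1 − 2ρ²/π) = 0.180, 0.206, 0.231; power 83%, 72%, 62%.

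**6. Wider range.** For ρ from 0.5 to 0.9 (normal approximation): main effect 63% down to 14%; own-baseline ANCOVA 90% down to 82%; stratum-only ANCOVA 86% down to 44%; interaction 82% throughout.

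**7. Follow-up hypothesis against Table 3.** The primary row is T2 only; row j is T2 minus T1; row 3c repeats the primary measure in completers, and the text places that comparison post-intervention. The mixed ANOVA text is confined to the other, secondary measures. Comfortable gait speed at T3 therefore has no primary or secondary comparison. Row 3b (GEE) covers primary and secondary outcomes at baseline, T2 and T3, but states no T3 contrast and no direction.

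**8. Row h against the hypothesis.** The hypothesis expects higher MLWP scores on the secondary measures; row h expects fewer daily steps under MLWP, without explanation. Row i, directly below, uses the same sign for staffing, where it makes sense.

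**The case against.** Five points can fairly be made in the plan's defence.

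- **Power.** A reader might infer that the mixed ANOVA itself costs a large share of the power. The article does not say that the group main effect is the test. The usual treatment test in a mixed design that includes baseline is group-by-time, which keeps about 82%. That is close to own-baseline ANCOVA, and about equal to or better than stratum-only ANCOVA, the only version the article describes. This stands: the low figures are conditional on the main effect being used, and the defect is that the term is unstated. Own-baseline ANCOVA is a recommendation, not something already planned.
- **Visit-specific estimates.** The Statistical Analysis section promises mean differences with confidence intervals for all models, and contrasts at T2 and T3 can be taken from a mixed ANOVA. True, though the text specifies none.
- **Scope.** A reader might infer that every secondary outcome is affected, or that comfortable gait speed is never analysed at follow-up. Rows i and j lie outside the conflict, and the GEE row does include comfortable speed at T3.
- **Row h.** A reader might infer that the step result could be declared positive either way. All tests are two-sided, so the estimate, interval and p-value do not change. Only the declared hypothesis does, and a sign slip is plausible.
- **Completers.** ANOVA in the text and ANCOVA in Table 3 may be one model under two names, because the Primary Analysis section calls a model with group and a two-level stratum an ANCOVA. This stands; the completer wording needs tidying but is not shown to be a conflict of method.

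None of this removes the difference between the text and Table 3 for rows a to h.

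**Conclusion.** The point holds. The article gives two different analyses for the same eight continuous secondary outcomes, names neither the test term in one nor the covariate in the other, and so leaves the choice open after the data are seen. Under the assumptions above, power for the same effect runs from roughly 25 to 55% (main effect, estimate 0.093 instead of 0.14 m/s) through about 82% (interaction) to 83 to 88% (own-baseline ANCOVA). The spread depends on assumed SDs, equal correlation between visits and an effect fully kept at T3. It shows that the choice matters, not that the trial will lose power.

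The hypothesis on comfortable gait speed at follow-up has no primary or secondary test, only sensitivity models without a stated T3 contrast. Row h contradicts the hypothesis in direction, with no effect on a two-sided p-value. The primary analysis and the sample size are untouched. This should be corrected, but it does not threaten the main result.

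**What to change.** 1. State one method, in identical terms, in the Secondary Analysis text and in Table 3 rows a to h: ANCOVA at T2 and at T3, with treatment, the outcome's own baseline value and the baseline speed stratum. Remove the mixed-design ANOVA from the text.
2. Add a secondary row to Table 3 for comfortable gait speed at T3, with the same model.
3. Reconcile the direction in row h with the hypothesis in the Background, or explain why daily steps are an exception.
4. Use one name and one model, that of the primary analysis, for the completer comparison in the Sensitivity Analyses text and row 3c.

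The cost is wording only. Table 2 already schedules each of these measures at baseline, post-intervention and follow-up, so no new data, visits or participants are needed. The change should be dated before any unblinded look at outcomes.

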**Methods/Design:**

A parallel, randomized controlled trial with stratification by baseline gait speed will be conducted. Allocation will be controlled by a central randomization service and participants will be allocated to the two active intervention groups (1:1) using a permuted block randomization process. Seventy participants will be assigned to one of two 15-session training programs. In MLWP, one physiotherapist will supervise practice of various overground walking tasks. Instructions, feedback, and guidance will be provided in a manner that facilitates self-evaluation and problem solving. In BWSTT, training will emphasize repetition of the normal gait cycle while supported over a treadmill, assisted by up to three physiotherapists. Outcomes will be assessed by a blinded assessor at baseline, post-intervention and at 2-month follow-up. The primary outcome will be post-intervention comfortable gait speed. Secondary outcomes include fast gait speed, walking endurance, balance self-efficacy, participation in community mobility, health-related quality of life, and goal attainment. Groups will be compared using analysis of covariance with baseline gait speed strata as the single covariate. Intention-to-treat analysis will be used.

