### Statistical Analysis

The trial results will be reported in accordance with the CONSORT criteria [http://www.consort-statement.org]. The flow of patients in the trial will be summarized using a flow-diagram. The baseline characteristics and outcomes scores of the patients will be analyzed using descriptive statistics reported by group as mean (standard deviation [SD]) or median (first quartile [Q1], third quartile [Q3]) for continuous variables depending on the distribution and count (percent) for categorical variables. Intention to treat analysis technique will be used for the primary analysis [71]. Missing data will be handled through multiple imputation technique [72]. All statistical tests will be performed using two-sided tests at the 0.05 level of significance. The Tukey's HSD method will be used to adjust the level of significance for testing for secondary outcomes. For all models, the results will be expressed as estimate of mean difference (or odds ratios for binary outcomes), standard errors, corresponding two-sided 95% confidence intervals and associated p-values. P-values will be reported to three decimal places with values less than 0.001 reported as < 0.001. Adjusted analyses will be performed using regression techniques to investigate the residual impact of key baseline characteristics on the outcomes (i.e. age, time since stroke onset, comfortable gait speed, and training site). Goodness-of-fit will be assessed by examining the residuals for model assumptions and chi-squared test of goodness-of-fit. All analyses will be performed using SPSS version 16.0 for Windows or SAS 9.2 (Cary, NC).

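### The text and Table 3 name different models for the same eight secondary outcomes (mixed ANOVA versus ANCOVA), and neither the governing model nor the ANOVA term that tests treatment is stated

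*Protocol article*

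**What the plan says.** All references are to the protocol article.

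- **Secondary Analysis** opens with this plan: "Mixed design analysis of variance will be used to compare the two groups' baseline, post-intervention and follow-up scores on all other secondary measures". It then adds "The two factors will be time and group". Baseline is therefore one of three outcome levels, and neither a baseline covariate nor the randomization stratum is in the model. The section does not say whether the group term or the group-by-time term tests treatment.
- **Table 3:** the block headed "2) Secondary (T2, T3") gives ANCOVA for rows a to h, for example "Fast Gait Speed (c") and "Six minute walk test(c"). Baseline is not among the outcome time points. Row i (trainers per session) has a t-test and row j (gait-speed responders) a chi-square test.
- **Sensitivity Analyses** gives the table its status: "Refer to Table 3 for a summary of the planned analyses".
- **Abstract, Methods/Design:** after listing the primary and secondary outcomes, it says "Groups will be compared using analysis of covariance with baseline gait speed strata as the single covariate". The Primary Analysis section uses the same two terms, group and speed stratum.
- **Statistical Analysis:** for every model, "the results will be expressed as estimate of mean difference", with standard error, 95% confidence interval and p-value.

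**The concern.** A table that summarises the planned analyses should match the text it summarises. Here the two name models that differ in the role of baseline, in the covariates and in the quantity estimated. The outcomes affected are fast gait speed, walking endurance, balance self-efficacy, dynamic balance, mobility participation, quality of life, goal attainment and daily steps. An analyst could follow either place and claim to have kept to the protocol. Within the ANOVA there is a second open choice between two terms that answer different questions. If these choices are settled after the data are seen, the result for any of the eight outcomes may depend on which route was taken.

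**Working it through.** **1. The plan's own figure.** The only sample size figure is for the primary outcome: difference 0.14 m/s, SD of change 0.19 m/s, two-sided 0.05, 80% power. n = 2 × (0.19 × (1.960 + 0.842) / 0.14)² = 28.91, so 29 per arm. 29 / 0.83 = 34.9, so 35 per arm and 70 in total. Both figures reproduce, and this point does not affect them. The protocol gives no power figure for the secondary outcomes.

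**2. What each ANOVA term estimates.** Let d0, d2 and d3 be the true group differences at baseline, T2 and T3. Randomization makes d0 = 0 in expectation.

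- Group main effect: (d0 + d2 + d3)/3 = (d2 + d3)/3. The mean post-treatment difference is (d2 + d3)/2, so the ratio is always 2/3. A constant difference D becomes 2D/3; on the primary outcome's scale, 0.14 becomes 0.093.
- Group-by-time: the contrasts are d2 − d0 and d3 − d0, which equal d2 and d3 in expectation. There is no dilution.

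Measured against the T2 difference alone, the main effect is 0.67 of it if T3 equals T2, 0.50 if T3 is half of T2, 0.75 if T3 is 1.25 times T2, and 0.83 if T3 is 1.5 times T2.

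**3. Power.** Assumptions: 29 analysed per arm (Sample size section), unit SD at each visit, the same correlation r between all visits, and a constant difference D at T2 and T3. The protocol gives no r, so 0.5 to 0.9 is shown. D is set so that ANCOVA at T2 on the outcome's own baseline has 80% power: D = 0.749 × √(1 − r²).

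- Main effect: the SD of a participant's mean is √((1 + 2r)/3). The noncentrality is (2D/3) / (SD × √(2/29)), on 56 df.
- Interaction: λ = 29 D² / (3(1 − r)), referred to F(2, 112).

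| r | D | Main-effect noncentrality | Main-effect power | λ | Interaction power |
|---|---|---|---|---|---|
| 0.5 | 0.649 | 2.02 | 51% | 8.13 | 71% |
| 0.7 | 0.535 | 1.52 | 32% | 9.22 | 77% |
| 0.9 | 0.326 | 0.86 | 13% | 10.30 | 82% |

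A simulation of 20,000 trials at r = 0.7 agrees: main effect 0.319, interaction 0.767, ANCOVA 0.790, and a mean group estimate of 0.667 D.

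**4. The ANCOVA as the protocol specifies it.** Where the protocol names a covariate for its ANCOVA, it names only the two-level speed stratum. Suppose, optimistically, that the stratum is a median split of the outcome's own baseline. The residual SD is then √(1 − 2r²/π). With the same D, power at T2 is about 75%, 67% and 42% at r = 0.5, 0.7 and 0.9. At r of 0.7 and above this is below the ANOVA interaction.

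**The case against.** The strongest answer is that group-by-time is the usual treatment test in a two-group design with baseline, post-treatment and follow-up scores. That test is undiluted. Its T2-minus-baseline and T3-minus-baseline contrasts yield mean differences and intervals, and the Outcomes section does speak of comparing change scores. The abstract's sentence is condensed, matches the primary model and does not name the secondary outcomes. Adjusted regressions that include baseline gait speed, and GEE over all three visits, are also planned. Finally, the 80% benchmark belongs to an ANCOVA on the outcome's own baseline, which the protocol does not specify.

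Most of this stands, and it limits the point:

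- A reader might infer that the planned ANOVA shrinks the treatment effect by at least a third. The protocol does not support that. It never names the group main effect as the treatment test. Against the T2 difference the shrinkage is also less than a third if the benefit grows by follow-up (25% if T3 is 1.25 times T2). The hypothesis gives no relative sizes.
- A reader might infer that the ANOVA cannot estimate the T2 and T3 differences. It can, through its contrasts, but the protocol does not name them.
- The abstract is only supporting evidence. The firm conflict is between the Secondary Analysis text and Table 3.

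None of this removes the conflict. The adjusted regressions and GEE supplement the main secondary analysis and do not decide between the two models. The weak stratum-only ANCOVA is a reason to state the covariates when the passages are aligned, not a reason to leave them as they are.

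**Conclusion.** The point holds as a contradiction between the text and Table 3 for rows a to h, with the ANOVA's treatment term also left open. The consequence is conditional. If the group main effect were used, it would be exactly one third below the mean post-treatment difference whatever the correlation. Its power would be about 32% (13% to 51%) where own-baseline ANCOVA has 80%; these power figures rest on the equal-correlation, constant-effect and 29-per-arm assumptions above. If the interaction were used, power would be about 71% to 82% and nothing would be diluted. The omnibus test would still be non-directional and would need the two contrasts with baseline to deliver the promised mean differences. Rows i and j, the primary analysis and the sample size are not affected.

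**What to change.** Replace the mixed ANOVA sentence in Secondary Analysis, and align Table 3 and the abstract with it, so that one model is named for rows a to h. Use either ANCOVA at each visit or a baseline-adjusted repeated-measures model for T2 and T3. Include treatment, the outcome's own continuous baseline value (not the speed stratum alone) and the speed stratum. Report the adjusted mean difference with its 95% CI at T2 and at T3 separately. Leave the t-test for row i and the chi-square test for row j.

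The cost is a few sentences, to be settled before anyone sees outcome data by group. No new data are needed, because Table 2 already schedules the measures behind rows a to h at baseline, post-intervention and follow-up.

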### Sample size

Seventy participants will be recruited. The sample size has been calculated to reliably detect a 0.14 m/s between-group difference in gait speed change (assuming a standard deviation of 0.19 m/s) with 80% power at a 2-tail significance level of 0.05. Using self-selected gait speed as the primary outcome, this sample size has been estimated based on a range of change scores and standard deviation values reported in the literature. Reported differences in change scores between experimental and control interventions range from 0.9 m/s to 0.14 m/s and standard deviation in change scores range from 0.14 to 0.19 m/s [19,33,34,69,70]. Using a conservative estimate of standard deviation of change score of 0.19 and a difference between group change scores of 0.14 m/s, the minimal number of participants required for each treatment group is 29 participants. Dropout rates in previous studies have ranged from 7 to 20% [19,33]. Allowing for a 17% loss to follow up rate, the study will need to recruit approximately 35 participants into each group for a total of 70.

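### Adverse-event testing is stated two incompatible ways: the text tests only differences that already look significant, Table 3 tests all seven event types by chi-square, including events likely to be sparse

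*Protocol article*

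**What the plan says.** The Secondary Analysis section begins with description: "Descriptive statistics (i.e. means, or frequencies) will be used to present data related to adverse and serious adverse events by groups". It then adds the testing rule: "Any apparently significant differences between groups will be analysed for significance using chi square statistics". It gives no threshold for when a difference qualifies.

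The Sensitivity Analyses section points to Table 3 as the overview: "Refer to Table 3 for a summary of the planned analyses". Under its secondary heading, Table 3 has a block headed "Adverse events (count" (closing bracket omitted here). The block has seven rows, from falls during a session down to "g) Death (all causes". Each row is typed as binary and each is given a chi-square test, with no condition attached.

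The general rules in the Statistical Analysis section are "All statistical tests will be performed using two-sided tests at the 0.05 level of significance" and "The Tukey's HSD method will be used to adjust the level of significance for testing for secondary outcomes". The article states no expected adverse-event rates.

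**The concern.** There are three linked problems.

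- **Conflict.** One statement tests every listed event. The other tests only those that stand out on inspection. An analyst cannot comply with both, and which safety p-values appear in the report would depend on a judgement made with the data in view.
- **Reading the p-values.** Under the text's rule, a safety p-value is seen only when the difference is already large. Among p-values selected in this way, values below 0.05 are more common than 5% even with no true difference.
- **Method for sparse events.** The article fixes chi-square for every event type, including those likely to affect very few of 70 people. In such tables a conclusion at 0.05 can depend on which version of the test is run.

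The arms differ in harness support, physical guidance and tolerance of error (Table 1), so falls and injuries bear on the comparison. A handful of events reported as a significant difference would be easy to over-read. The unit is also loosely stated, because the block heading speaks of counts while the rows are binary.

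**Working it through.** **Inputs.** From the Sample size section: "0.14 m/s between-group difference in gait speed change (assuming a standard deviation of 0.19 m/s) with 80% power", two-sided alpha 0.05, 29 per group, 17% loss, 35 per group recruited. From Table 3: seven adverse-event rows. Assumed, because the article gives none: event rates of 1% to 30% per arm, and a numerical stand-in for the look-first condition.

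**1. The plan's own figure.** n per arm = 2(1.96 + 0.842)² × 0.19²/0.14² = 2 × 7.85 × 1.842 = 28.9, so 29. Allowing for loss: 29/0.83 = 34.9, so 35 per arm and 70 in total. This reproduces. Each safety table therefore has about 35 per arm.

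**2. When cells are sparse.** With equal arms, the expected event count per arm is (total affected)/2. It reaches 5 only when at least 10 participants are affected, and 10/70 = 14%.

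**3. Single tables at 35 per arm.** The uncorrected statistic is N(ad − bc)²/(product of the four margins). For a 4-0 split: 70 × (4 × 35 − 31 × 0)²/(35 × 35 × 4 × 66) = 1,372,000/323,400 = 4.24, p = 0.039. Fisher's exact p = 2 × C(35,4)/C(70,4) = 2 × 52,360/916,895 = 0.114. Other splits by the same methods:

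| Split | Uncorrected chi-square | Continuity-corrected | Fisher |
|---|---|---|---|
| 4-0 | 0.039 | 0.122 | 0.114 |
| 5-0 | 0.020 | 0.063 | 0.054 |
| 6-1 | 0.046 | 0.111 | 0.106 |
| 7-1 | 0.024 | 0.060 | 0.055 |
| 8-2 | 0.040 | 0.088 | 0.084 |

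**4. Size of one pre-chosen test.** This is found by exact enumeration over two independent binomials with 35 per arm and equal true rates, summing the probability of tables with p < 0.05.

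| True rate | Uncorrected chi-square | Fisher |
|---|---|---|
| 1% | 0.001 | 0.000 |
| 5% | 0.036 | 0.003 |
| 10% | 0.057 | 0.013 |
| 15% | 0.053 | 0.022 |
| 20% | 0.049 | 0.025 |
| 30% | 0.051 | 0.028 |

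The uncorrected test is below nominal at the low rates and exceeds 5% by at most 0.7 percentage points.

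**5. Effect of looking first.** Suppose a test is run only if the arms differ by at least 3 participants. With no true difference:

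| True rate | P(test is run) | P(p < 0.05, given a test) | Product: unconditional |
|---|---|---|---|
| 5% | 0.161 | 0.225 | 0.036 |
| 10% | 0.313 | 0.184 | 0.057 |
| 20% | 0.453 | 0.107 | 0.049 |
| 30% | 0.514 | 0.098 | 0.051 |

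The last column equals the sizes in step 4, so the condition creates no extra rejections. What changes is the meaning of a p-value that gets reported: between 10% and 23% of those run fall below 0.05 under no difference. With an assumed trigger of 2 participants the range is 7% to 11%; with 4 it is 14% to 67%.

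**6. Testing all seven.** If the seven tests were independent and each at 0.05, the chance of at least one false positive would be 1 − 0.95⁷ = 30%. Tukey's HSD compares several group means. It does not adjust a set of two-group tests on different binary events.

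**The case against.** The strongest reply is that little harm follows. A reader might infer that looking first inflates the false-positive rate. It does not: screening can only remove tests, and step 5 shows the same unconditional rate with and without it. A reader might also infer that chi-square is badly anti-conservative with so few events. On average it is not: it is below nominal at rates of 1% and 5%, and part of the gap to Fisher is Fisher's own conservatism. Both replies stand, so neither stronger reading is made here.

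The contrast in single tables also assumes an uncorrected statistic. The article does not say which form is meant, and with continuity correction the results lie close to Fisher. A small-cell fallback could properly sit in an analysis plan that is not shown, so its absence is not the complaint. The point is that the article assigns one test to all seven rows.

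One could read Table 3 as naming the method and the text as saying when to use it. That is possible, but the table carries no condition and is offered as the summary of what is planned, so the reader is left to guess. The descriptive presentation by group does mean that no event is hidden, which limits the damage.

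A further tempting inference is that repeat falls by one person would be tested as independent events. The article does not support this. Both fall rows are typed binary, and the heading's wording fits the article's general convention of summarising categorical variables by count and percentage. Only the label needs tidying.

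**Conclusion.** The concern holds as a minor point. The text and Table 3 give different rules for which adverse events are tested. The text's rule is undefined and applied after seeing the data, so p-values reported under it do not carry their nominal meaning. Where fewer than 10 of 70 participants are affected, the choice between uncorrected chi-square and Fisher can decide whether a split such as 4-0 or 6-1 is called significant.

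The documents do not support a claim of large type I inflation: the per-test size is at most about 0.057 over the rates tried.

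This rests on three assumptions. Sparsity is assumed for myocardial infarction, new stroke and death over a program of up to seven weeks plus eight weeks of follow-up; falls or hospitalizations could well reach 10 participants, where chi-square is acceptable. The rates of 1% to 30% are assumed. The numerical triggers in step 5 are stand-ins for a condition that the article leaves undefined. The primary analysis and the sample size are unaffected.

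**What to change.** - In Secondary Analysis, keep the sentence on descriptive presentation and delete the conditional testing sentence, so that the text and Table 3 treat all listed events alike.
- For each of the seven events, report the number of participants with at least one event in each arm and the risk difference with a 95% CI.
- If p-values are given, use Fisher's exact test for all seven events, change the method column of Table 3 to match, and state that these p-values are unadjusted and exploratory.
- Change the heading of the Table 3 block from a count to participants with at least one event, in line with the binary typing of its rows.

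A rate model for recurrent falls, such as negative binomial, is an optional addition and not part of this correction.

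The cost is wording only. The downside is that Fisher's test is conservative (size 0.003 at a 5% event rate and 0.013 at 10%, 35 per arm), so the risk difference and its interval should carry the interpretation.
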